## ii. Trial Funding

This trial is part of a JPND funded consortium awarded in 2022 (Call: "Understanding the mechanisms of non-pharmacological interventions", JPND2022-128)

## 3. Background

Parkinson's disease (PD) affects over 10 million people worldwide and is one of the most prevalent neurodegenerative diseases. It is a multi-system neurodegenerative disorder, which among other symptoms causes severe and disabling motor deficits. One of these deficits, impaired gait, causes falls, a serious complication for people living with PD, even when managed with medication. Approximately 70% of people with PD experience falls each year. The consequences of falls include fractures, hospital admissions, increased caregiver burden, loss of independence, fear of falls, social isolation and early mortality. Falls are cited as one of the worst aspects of PD and unfortunately only few efficacious interventions are available. Non-pharmacological interventions in the form of exercise contribute to slowing disease progression and reduce fall risk through substantial improvements in gait quality, as reflected in increased speed and stride length and reduced gait variability.

Improving walking ability and preventing falls in people with PD is of critical importance to the world's aging population and health care systems globally. The importance of improving gait and preventing falls for people with PD and their communities is corroborated by our early stakeholder survey. This survey (used in the co-development of this project) included 294 people with PD, 76 family members, 16 clinicians and 29 caregivers. It revealed strong consensus regarding the imperative to develop effective gait training interventions that can improve walking ability, reduce fall risk; and increase quality of life. However, because of gaps in our mechanistic understanding, most exercise prescription fails to address the unmet needs and motor deficits specific to PD. People living with PD walk with short strides and consequently, at a slow speed, which is associated with poor general health. Their gait pattern is further characterized by a high variability of step characteristics, which is associated with falls.

Fortunately, training can increase stride length and gait speed and reduce variability. Treadmill training may provide a response to the unmet needs of people with PD and their community. Generally, exercise interventions targeting gait are effective and more effective than other exercise interventions, in reducing falls rate and improving gait performance and even reducing freezing of gait. Specifically, treadmill training has been shown to be safe and beneficial, and training effects may be enhanced by adding mechanical perturbations and virtual reality. Mid-tier treadmills range from €350 to €1,350 and some models can fold away making them practical even in the home situation. Treadmill training is unaffected by inclement weather, can be undertaken several days per week and may be implemented in parallel with pharmacological treatments.

Therefore, the interventions studied here will consist of treadmill training, including the application of mechanical perturbations and virtual reality to destabilize gait and trigger gait adaptations. To optimize and personalize treadmill training, it is essential to disentangle how people with PD benefit from treadmill training. To this end, we will relate the positive outcomes of this well-proven non-pharmacological intervention to kinematic, neurophysiological, and psychological changes. We will determine the effects of treadmill training in people with PD at four levels: primary clinical outcomes, feedback control of centre of mass (CoM) movement, neural correlates of feedback control, and mediation of transfer to daily-life gait. In addition, we will explore which factors determine individual outcomes at each of these levels.

## 4. Rationale, objectives, and endpoints

### i. Rationale

The **rationale** of this trial is that speed dependent treadmill training (SDTT) improves gait through improved sensorimotor integration, with changes in cortical activity as neural correlates. Additional benefits of treadmill training can be seen if perturbation or adaptations are added. This is based on the idea, that in addition to the sensorimotor integration the reactive balance is trained as well. Furthermore, it hypothesizes that treadmill training and its effects on gait quality will improve gait self-efficacy, which mediates and/or modifies transfer of training effects to improved daily-life gait.

### ii. Objectives

Thus, the **objectives** of our StepuP project are:

1. To understand the kinematic and neural mechanisms that underlie improvements in gait due to treadmill training with and without mechanically and VR-triggered gait adaptations in people with PD;
2. To assess to what extent improvements in gait due to treadmill training, as measured in the lab, transfer to improvements in daily life mobility;
3. To understand the mechanisms that underpin transfer from improvements in gait to improvements of mobility in daily life in people with PD;
4. To understand for whom treadmill training improves lab-based gait characteristics and for whom it does not, and understand for whom treadmill training improves mobility in daily life and for whom it does not.

Attaining these objectives will provide a better understanding of the successes and failures of treadmill training to improve gait stability and prevent falls in people with PD at an individual level, which in the medium term will allow targeted delivery of such interventions and in the long term will allow personalization of such interventions to improve outcomes for all.

### iii. Endpoints

Concerning **the endpoints**, this trial examines the effect of treadmill training with and without perturbations on comfortable overground gait speed, and neural correlates in people with PD. The **primary endpoint** is (change in) gait speed, **secondary endpoints** are divided into three groups (clinical, kinematic and neurophysiological). Clinical measures are used to assess the effect of training on disease symptoms. Kinematic measures are changes from baseline to follow-up, all under controlled conditions (treadmill), and provide insight into gait performance and quality. Neurophysiological measures aim to understand the neural control mechanisms underlying the training effects. On an **exploratory level**, the study aims to assess the training effects on daily-life gait by using wearable devices and assess gait self-efficacy using previously validated questionnaires.

## 5. The StepuP trial design

### i. Study design

StepuP is a multicenter non-pharmacological randomized controlled trial (RCT) conducted at four clinical centers: Christian-Albrechts-Universität zu Kiel (Kiel), Tel Aviv Sourasky Medical Center (Tel Aviv), University of New South Wales (Sydney), IRCCS Istituto delle Scienze Neurologiche di Bologna (Bologna). 42 PwPD will be enrolled and will be randomized into an intervention group (IG) and a control group (CG) at the clinical sites in Kiel and Sydney. 21 PwPD will be enrolled in Tel Aviv and Bologna and randomized as well into an IG and CG. All Participants will receive a 2-6 week speed-dependent treadmill training (SDTT) aimed at improving gait. Subjects in the IG will receive the same STDD with additional perturbations (SDTT+). Baseline (To) and follow-up (T1 & T2) visits include descriptive, clinical, kinematic and neurophysiological assessment. A 7-day home monitoring with digital sensors will be performed before To and after T2. In Sydney half of the patients in the CG and half of the patients in the IG will have also a second baseline measurement before receiving the SDTT.

### ii. Specific Workpackages

The work within the trial will be broken down into specific work packages (WP), into which the sites mentioned above and other two other sites (Vrije Universiteit Amsterdam, [name]. [name], [[contact]](mailto:[contact]) (Amsterdam) and Swiss Federal Institute of Technology, [name], [[contact]](mailto:[contact]) (Zürich)) contribute. The WP are explained in more detail in the following. Please note that only the clinical centers (Bologna, Kiel, Sydney and Tel Aviv) conduct active recruitment and training, and therefore seek for ethical approval. Figure 1 shows the interaction between WP.

**Figure 1: Overview of WPs of StepuP, and the interaction between them.**

[figure not shown]

#### A. WP1: Gait improvements after treadmill training

WP1 aims to investigate the gait improvements after treadmill training in patients with Parkinson's disease (PwPD) at four clinical sites (Bologna, Kiel, Sydney, Tel Aviv; WP leader: Kiel). A total of 126 patients will be recruited and undergo training with or without mechanical perturbations or virtual perturbations.

## **B. WP2: Mechanisms underlying gait improvements after treadmill training**

This WP (Amsterdam, Bologna, Kiel, Sydney, Tel Aviv; WP leader: Amsterdam) aims to support clinical centers in setting up standardized data collection procedures and to study the factors underlying improvements in primary outcomes related to gait PwPD. The protocol involves assessing lower body kinematics, EMG activity, and EEG data during treadmill training to test the hypothesis that improvements in gait are due to an improved coordination of foot placement to center of mass movement, which is related to better sensorimotor integration. The trial also aims to assess cortical control of locomotion in people with PD and correlate changes in behavioral measures with changes in neural measures. Statistical analyses will focus on correlating changes in primary outcomes with changes in behavioral and neural measures.

## **C. WP3: Daily-life mobility changes after treadmill training**

This WP (Bologna, Kiel, Sydney, Tel Aviv, Zürich; WP Leader: Zürich) will analyze the effects of treadmill training on daily-life mobility, focusing on gait quality and physical activity using data from body worn inertial sensors for a week at each time point. The analysis will compare the effects of lab-based training versus real-world training, and examine the relationship between improvements in lab-based gait outcomes and daily-life gait outcomes. The collected data will be used to extract parameters such as gait speed, stride length, and number of steps, and will be analyzed using linear mixed effects models with repeated measures over time. The analysis will also investigate whether gait self-efficacy mediates the effects of lab-based gait improvements on daily-life gait outcomes.

## **D. WP4: Patient engagement and understanding individual responses to treadmill training**

The goal of WP4 (Amsterdam, Bologna, Kiel, Sydney, Tel Aviv, Zürich; WP Leader: Sydney), is to combine qualitative interview data with quantitative data from WPs 1-3 to understand why treadmill/enhanced training may improve lab-based gait outcomes and daily-life gait outcomes in some people but not others, and to identify barriers and facilitators to uptake of treadmill training protocols. The team will establish a secure, cloud-based computing environment for GDPR-compliant collection, curation, and analysis of sensitive data. Machine learning will be used to investigate the relative importance of various factors for successful intervention outcomes. The qualitative analysis will provide important insights into barriers and enablers to ongoing treadmill training for developing more personalized and effective therapies to improve walking and prevent falls in people with PD.

## **E. WP5: Management and ECR training**

This work package (Amsterdam, Bologna, Kiel, Sydney, Tel Aviv, Zürich; WP Leader: Amsterdam) focuses on project management for the proposed trial on non-pharmacological interventions. The coordinator will oversee project progression and ensure compliance regarding legal and ethical issues, timely action for foreseen or unforeseen risks, and the fulfillment of goals with respect to dissemination, data and code sharing, gender balance, and early-career researcher support. The project will follow data protection and ethical guidelines, use the Brain Imaging Data Structure (BIDS) standard to store motion, EMG, and EEG data, and establish a Github repository for code sharing. The risks of the project are discussed, and working groups will be established to minimize risks. The package also includes support for early-career researchers, including joint supervision, structured research visits, and active involvement in all aspects of the project. ECR workshops on open science will be organized, with training on clinical assessment of patients during the first in-person workshop.

### **iii. Participants**

Participants will be enrolled within the study across the four clinical centers on the basis of the following inclusion and exclusion criteria (Table 1):

## **A. Inclusion criteria**

1. Diagnosis of PD according to the MDS Criteria
2. Hoehn and Yahr stages I to III;
3. Movement Disorder Society-sponsored version of the Unified Parkinson Disease Rating Scale (MDS-UPDRS) gait sub-score of 1 or more
4. Signed informed consent to participation

## **B. Exclusion criteria**

1. Any known general health condition likely to interfere with or to pose a contraindication to physical exercise (e.g., severe heart disease, severe chronic artery disease, orthostatic hypotension according to guidelines, chronic respiratory problems, subjective or objective vertigo, relevant orthopedic and other diseases such as recent lower limbs fractures limiting weight bearing, etc.). For screening and assessment purposes, the 2023 version of the Physical Activity Readiness Questionnaire, extended version (PAR-Q+) will be administered, together with Electronic Physical Activity Readiness Medical Examination (ePARmed-X+) in case of positive screening. Subjects will be excluded if, they are not cleared for engaging in physical activity or are cleared only for medically supervised physical activity.
2. Moderate or severe depression (defined as scores of  $\geq 18$  on the Beck Depression Inventory [BDI])
3. Cognitive impairment which may preclude the possibility to provide a fully informed consent to enrollment, as indicated by elements of temporal or spatial disorientation which may be revealed within ordinary conversation or by a confirmed diagnosis of cognitive decline (e.g., Levy-Body Dementia). In case of doubt, the Six-item Cognitive Impairment Test (6CIT, pass cutoff score  $> 9$ ) will be administered.
4. Linguistic comprehension capacity less than 75% in ordinary conversation due, for instance, to an aphasic impairment or to severe deafness notwithstanding the use of an acoustic aid. In case of doubt, a simple test of linguistic comprehension (token test) will be administered before enrollment.
5. Severe psychiatric comorbidity which may interfere with compliance to the study protocol (e.g., a known diagnosis of personality disorder, documented previous occurrences of delirium and psychomotor agitation).
6. History of or status of substance dependency
7. Implanted Deep Brain Stimulation device

**Table 1: Inclusion and exclusion criteria for participation in the StepuP trial**

| Inclusion Criteria                                                                                                                                                                                                       | Exclusion Criteria                                                                                                                                                                                                                                                                                                                                                                                                                                                                                                                                                                                                                                                                                  |
|--------------------------------------------------------------------------------------------------------------------------------------------------------------------------------------------------------------------------|-----------------------------------------------------------------------------------------------------------------------------------------------------------------------------------------------------------------------------------------------------------------------------------------------------------------------------------------------------------------------------------------------------------------------------------------------------------------------------------------------------------------------------------------------------------------------------------------------------------------------------------------------------------------------------------------------------|
| 
 
- PD according to the MDS Criteria
 
- H&Y I-III
 
- MDS-UPDRS gait subscore <math>\geq 1</math>
 
- Signed informed consent to participation
 
 | 
 
- Any known general health condition likely to interfere with or to pose a contraindication to non-medically supervised physical exercise.
 
- Moderate or severe depression (BDI-II <math>\geq 18</math>)
 
- Cognitive impairment which may preclude the possibility to provide a fully informed consent to enrolment.
 
- Linguistic comprehension capacity less than 75% in ordinary conversation
 
- Severe psychiatric comorbidity which may interfere with compliance to the study protocol
 
- History of or current status of substance dependency
 
- Implanted Deep Brain Stimulation device
 
 |

*PD – Parkinson, MDS - Movement Disorder Society, UPDRS Unified Parkinson’s Disease Rating Scale, H&Y - Hoehn and Yahr, BDI-II - Beck Depression Inventory-II*

#### iv. Participant schedule

Each participant will undergo a total of four phases subsequent order. An overview can be found in Figure 2. Overview participant’s schedule.

##### **Pre-Training**

The Pre-Training phase including *screening, enrolment, home assessment and functional assessment (T0)* will last for two weeks. There should not be more than 14 days between the enrolment and the start of the first training visit. In Sydney, half of the patients who are randomized into the control group and half of those who are randomized into the intervention group, will undertake a second baseline measurement; thus, their *Pre-Training phase* will be extended by 6 weeks. Within these 6 weeks  $\pm 1$  week, participants will have undergone the second baseline measurement.

##### **Training**

The *training* will consist of 12 sessions in total. There can be 0-4 days break between any training session depending of the state of the participant and logistics at each centre.

##### **Post-Training**

The Post-Training phase including *home assessment and functional assessment (T1)* will last for a total of 14 days. There should not be more than 2 days between second functional assessment and the end of the last training visit. Also, the home-assessment should not start later than 5 days after the second functional assessment.

##### **Follow-Up**

The Follow-Up visit (**T2**) will include a *functional assessment* and take place 12 weeks ( $\pm 2$  weeks) after the completion of the Post-Training phase.

**Figure 2.** Overview participant's schedule.[figure not shown]

*The Trial consists of a Pre-Training phase including screening, enrolment, home assessment and functional assessment (T0) and a possible second baseline measurement, a Training phase (12 training visits), a Post-Training phase including home assessment and functional assessment (T1) and a Follow-up phase including home assessment and functional assessment (T2).*

## v. Screening

PwPD: Patients admitted to each of the four clinical centers as in- or out-patients will be invited to participate. Potential candidates can be approached via registries and hospital records (given that they gave priori consent to be contacted for future research) or flyers and local advertisements.

The clinical partner in Kiel can obtain data from clinical routines due to the broad consent statement of a patient which has been hospitalized in the past. In Kiel potential candidates will receive patient information, and the consent form digitally prior to screening.

## vi. Enrolment

All interested potential participants will attend a screening appointment. This will consist of signing the informed consent, and then reviewing / evaluating the inclusion and exclusion criteria. Prior to signing the informed consent, each person is given sufficient time to consider whether to participate in the study. The researcher must assess that the participant can give consent for themselves. If the assessment does not reveal adequate capacity of the participant, the investigator must usually either exclude the potential participant from the study or seek surrogate consent for their participation. It is made clear to the potential participant, that participation is completely voluntary, and as such they are free to decide to stop participation at any moment without any consequences.

Concerning informed consent, the staff member taking the consent will confirm that the potential participant has read the information sheet before discussing the study further and answering any questions they may have. If the potential participant agrees to participate, they will be asked to sign and date the consent form. This will be witnessed by the researcher taking the consent, who will also sign and date the form. The original consent form is kept in the site file and a copy is given to the participant.

During the preliminary contact, the PI or their delegate (recruiter) will ask the potential candidate if interested in receiving information about the possibility to participate in a non-pharmacological interventional research protocol involving patients with Parkinson's Disease. In case of a positive answer, the recruiter will obtain a consent for communicating the contact information of the patient to the recruiting team. Recruiters will review the inclusion/exclusion criteria in consultation with a trained neurologist.

The *enrolment* can be completed immediately after *screening*. If this is not completed as a single visit, the visit will be completed within 5 days after the *screening* visit.

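### The enrolment section offers surrogate consent as an alternative to exclusion, although the eligibility criteria bar, without exception, patients whose cognitive impairment may preclude informed consent

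*Protocol*

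**What the plan says.** Three places in the protocol set the eligibility rule.

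- Section 5.iii.A, inclusion criterion 4, requires "Signed informed consent to participation". No legal representative or surrogate is mentioned.
- Section 5.iii.B, exclusion criterion 3, removes patients with "Cognitive impairment which may preclude the possibility to provide a fully informed consent to enrollment", with no exception.
- Table 1 repeats this as "Cognitive impairment which may preclude the possibility to provide a fully informed consent to enrolment", again with no exception.

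Section 5.vi (Enrolment) sets the procedure. The screening visit consists of "signing the informed consent, and then reviewing / evaluating the inclusion and exclusion criteria". On capacity it states: "The researcher must assess that the participant can give consent for themselves". If that assessment finds capacity inadequate, "the investigator must usually either exclude the potential participant from the study or seek surrogate consent for their participation".

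Exclusion 3 also contains a rule for doubtful cases: "In case of doubt, the Six-item Cognitive Impairment Test (6CIT, pass cutoff score" > 9). The protocol gives neither the direction nor the range of the scale.

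**The concern.** The criteria and the enrolment procedure give different instructions for the same person. Under exclusion 3, a candidate who cannot consent because of cognitive impairment is out. Under the enrolment section, exclusion is one of two options, and the other is participation through a surrogate. The word usually loosens the instruction further, because it implies that some third, unstated course is open.

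The trial recruits at four clinical centres in four countries (Kiel, Tel Aviv, Sydney and Bologna). If one site works from Table 1 and another from the enrolment section, they can reach opposite decisions on identical candidates. What is at stake is mainly uniform eligibility and the protection of a vulnerable group; section 7.i commits the trial to Good Clinical Practice and the Declaration of Helsinki. A further reason for clarity is that participants must keep a diary, complete self-report scales such as the mGES, and carry out self-paced app walking at home.

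**Working it through.** No arithmetic applies; the check is a comparison of the passages.

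1. **Take a candidate found to lack capacity because of cognitive impairment.** Exclusion 3 and Table 1 both apply and both exclude. Inclusion 4 asks for signed consent and provides for no other signatory.

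2. **Apply the enrolment section to the same candidate.** A site that chooses exclusion complies with every passage. A site that chooses the surrogate route follows the enrolment section, and the criteria are reviewed next. If exclusion 3 is then enforced, the candidate leaves and the surrogate clause has achieved nothing. If it is not enforced, the candidate takes part against a stated criterion. For this candidate the clause is therefore either idle or in conflict with exclusion 3. The protocol does not say that exclusion 3 overrides it.

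3. **Look for an eligible group that the clause could serve.** Capacity might be lacking for reasons other than cognition. Poor language comprehension and severe psychiatric comorbidity have their own exclusions (criteria 4 and 5). These may not cover every cause, but the protocol names no eligible group that needs surrogate consent.

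4. **Look for a surrogate procedure.** The signing steps in section 5.vi involve only the participant and the researcher. Who may act as surrogate, how that person signs and what the participant is asked are not described.

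5. **Read the 6CIT rule separately.** Two things are open: whether passing means being eligible or going beyond the cutoff, and whether a higher score is better or worse.
   - Above 9 means eligible, and higher is better: coherent.
   - Above 9 means eligible, and higher is worse: reversed.
   - Above 9 means excluded, and higher is worse: coherent.
   - Above 9 means excluded, and higher is better: reversed.

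   The text does not select among these four. The rule meant to settle doubtful cases therefore does not say who is excluded.

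**The case against.** The strongest reply is that the order of events protects the criterion. Consent comes first, and the criteria are then evaluated with a neurologist's input, so surrogate consent does not by itself enrol anyone. The enrolment section also requires the researcher to establish that participants can consent for themselves, and it lists exclusion first. With no surrogate procedure behind it, the clause reads like leftover generic consent text. Most of this stands, and it limits the practical effect. It does not remove the conflict, because the sentence offers surrogate consent for participation itself, as the alternative to exclusion, and it remains operative text.

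Four stronger readings are tempting, and the protocol does not support them.

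- A reader might infer that the protocol actually admits these patients. It offers a route, but the later eligibility review can still close it.
- A reader might infer that everyone to whom the clause applies already meets exclusion 3. That criterion concerns cognitive impairment only, and capacity can be lacking for other reasons.
- A reader might infer that the 6CIT cutoff is printed backwards and misclassifies every doubtful case. That needs a scale direction the protocol does not give. The test's name hints that higher means more impaired, but passing can also mean exceeding, which is a natural reading inside an exclusion criterion.
- A reader might infer material harm to participants or to the mGES mediation analysis. Treadmill walking is harnessed with a clinician present, only the intervention arm receives perturbations, and app use is supported. The affected group is of unknown size and may be empty.

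**Conclusion.** The inconsistency is established by the protocol's own wording. For a candidate without capacity through cognitive impairment, the eligibility criteria say exclude, whereas the enrolment section says exclude or seek surrogate consent, and no passage reconciles the two. This conclusion needs no outside source and no assumption about the 6CIT.

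Its size in patients cannot be stated, because the protocol gives no figure for such candidates. Nothing indicates that the primary endpoint, the sample size or the primary analysis depends on it. It should be corrected because it concerns consent in a vulnerable group and because the sites need a single rule.

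The 6CIT wording is a secondary request for clarification. It is ambiguous, not shown to be wrong.

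**What to change.** Reconcile inclusion 4, exclusion 3, Table 1 and section 5.vi so that one rule applies at all sites. Because the three eligibility statements already agree, the simplest consistent change is in section 5.vi: remove the surrogate-consent alternative and the word usually, so that inadequate capacity leads to exclusion. If the sponsor does intend surrogate consent, the exception must be written into exclusion 3, Table 1 and inclusion 4, and a surrogate procedure must be described. That choice is the sponsor's.

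Separately, restate the 6CIT rule in exclusion 3 as a condition for exclusion, with the direction of the scale given.

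The cost is one sentence in section 5.vi and one in exclusion 3, submitted as an amendment. The downside of removing the clause is that a few candidates who might have entered through a surrogate are not enrolled; those lacking capacity through cognitive impairment are already excluded by the criteria.
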